### Outcomes

#### Clinical and radiographic evaluations

The teeth will be clinically and radiographically evaluated at 12 and 24 months regarding the pulp response [28–30]. During the follow-up assessment, the following clinical criteria will be verified: spontaneous pain; any signs of mobility, sensitivity to percussion, abscess/fistula, gingival swelling not caused by poor oral hygiene, and restoration failure. The radiographic criteria will include presence/absence of internal/external resorption, signs of furcal impairment, advanced rhizolysis stage, and restoration failure including fracture and loss. Two previously trained and calibrated blinded examiners will perform the clinical and radiographic assessments. Examiners will be previously trained and calibrated in relation to the clinical and radiographic criteria in a pilot study, based on previous studies [30, 31, 33]. Inter- and intra-examiner reliability will be verified by casual and systematic error [36]. The examiners will fill in a form with all data for further analyses of the results.

#### Measurement of the dentin barrier

After the scanning of the radiographs, the images will be analyzed in Image J2 software version 64 bits (National Institutes of Health, NY, USA) [37]. The measurements on the digitized radiographs will be performed at the immediate postoperative period and 12 and 24 months of follow-up. All measurements of the scanned images will be performed by a trained and calibrated examiner blinded to the clinical procedure and the pulp capping materials to perform the measurement of dentin barrier thickness, and points will be marked on the center of the capping material layer (point A) and on the center of the furcal area (point B) [37]. Intra-examiner calibration will be determined by the casual and systematic error [36]. To assure reproducibility, each image will be measured twice at 15-day interval. The mean of these two measurements will be used for the comparisons.

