### Interventions

#### Clinical procedures

All clinical procedures of this study will be performed by one previously trained and calibrated operator (post-graduate student). A detailed anamnesis and clinical examination will be performed. Next, an intraoral clinical examination with the aid of dental mirror and air jet will screen eligible molars. Then, a periapical radiograph of the eligible primary molars will be taken to verify the furcal conditions. Satisfying all inclusion criteria of the study and after informed consent is given, treatment will be randomly provided in the second visit, according to previously described allocation. The patient and legal guardians will remain blinded regarding the treatment type [32].

After tooth prophylaxis with rubber cup and prophylactic paste (Herjos Tutti Frutt, Vigodent, São Paulo, Brazil), washing, and drying, local anesthesia will be applied (articaine 4% + epinephrine 1:100.000) [28–31]. The cavity preparation will be performed under rubber dam isolation, using water-cooled diamond burs, and caries will be completely removed from the lateral walls and enamel-dentine junction with the aid of low speed round burs (KG Sorensen®, São Paulo, Brazil). The pulp chamber roof will be removed with the aid of round diamond burs (1014-1015) at high speed under copious irrigation. The coronal pulp will be removed with the aid of hand excavators. Pulp vitality will be checked by cut resistance, red color, and hemostasis after 5 min. If necessary, constant irrigation will be performed with sterile saline solution. Pulp stumps will be dried with sterile cotton pellets, and the capping material will be applied according the assigned group [28–31]:

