Control group—MTA (Angelus®, Londrina, Paraná, Brazil) will be mixed on sterile glass plate according to the manufacturer’s instruction (1 powder spoon to 1 drop of distilled water) for 30 s and placed onto the pulp stumps with the aid of spatula and sterile cotton pellet moistened with distilled water. A thin layer of the material will be assured, based on previous studies [14, 30, 31, 33, 34].BBio group—the dentin-pulp biostimulation chitosan membranes will be previously prepared in the laboratory with equal parts containing 1.5 g of chitosan (Sigma Aldrich, St. Louis, USA), 1.5 g of alginate, and 1.5 g portland cement-based. Each layer will be individually placed and dried at 30 °C for 15 min. Then, the membrane (composed of three layers) will be dried for more 24 h [25, 26]. After preparation and sterilization, the membrane will be placed on the pulp stumps.

For both groups, a thin layer of liner material (Cimpat white – Septodont, Pomerode, Santa Catarina, Brazil) will be placed onto the study materials, inside the pulp chamber. The final restorations will be performed with resin-modified glass ionomer cement (Vitremer® 3M/ESPE) [28–31]. Just after vital pulp therapy, a periapical radiograph will be taken (immediate postoperative radiograph) [28–30]. The follow-up periods will be 12 and 24 months after treatment [31, 35] (Fig. 1).

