The limitations of the present study include the disadvantages of noncompliance and high dropout rates, and the obstacle to control the period of follow-up. These disadvantages result in investigations with small sample size and the follow-up time. Further studies should be conducted, and the results should be confirmed through longer-term follow-up periods. The measurement of the dentin barrier after procedures of pulp therapy may have some limitations. This method will be used to avoid mistaken measurements due to the difficulty in evaluating the exact thickness of the dentin barrier and the overlapping of the radiographic image of the roots. One other bias of this present study will be the blinding of the operator. Although it is not possible to blind the operator during capping material application, we believe that this will not interfere in the study outcomes. Therefore, this study protocol aims at new perspectives of vital pulp therapy of primary teeth by employing new easy-handling, low-cost materials to keep viable the pulp tissue capable of regenerating and maintain the physiological process of deciduous tooth exfoliation.

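### The variable called dentin barrier thickness is a capping-material-to-furcation distance: it is above zero before any barrier exists and should not be read as barrier thickness

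*Protocol article*

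**What the plan says.** In the protocol article, under Measurement of the dentin barrier, a blinded examiner marks points on the scanned radiographs "to perform the measurement of dentin barrier thickness". The landmarks are given in the same sentence: "points will be marked on the center of the capping material layer (point A) and on the center of the furcal area (point B"). The article implies, without quite saying so, that the value is the distance A-B. The measurements "will be performed at the immediate postoperative period and 12 and 24 months of follow-up". The Abstract also promises that the thickness of the barrier will be assessed.

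Clinical procedures sets out what happens to the tooth. "The coronal pulp will be removed with the aid of hand excavators". MTA is placed onto the pulp stumps, and in the other arm "the membrane will be placed on the pulp stumps". The baseline film follows at once: "Just after vital pulp therapy, a periapical radiograph will be taken (immediate postoperative radiograph").

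Statistical methods compares the radiographic measurements over time by paired t test and between groups by independent t test. It does not say whether the between-group test uses the value at a visit or the change from the immediate film.

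The Discussion acknowledges that the measurement may have limitations and gives a reason for the choice: "This method will be used to avoid mistaken measurements due to the difficulty in evaluating the exact thickness of the dentin barrier". It adds the overlap of the root images as a further difficulty. Nowhere is A-B renamed or described as a surrogate.

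**The concern.** A barrier thickness should be zero when there is no barrier and should grow as one forms. A-B does not meet the first condition, and nothing in the article shows that it meets the second. One end of the line lies inside the capping material and the other at the furcation, so the reading includes material and dentin that were present before any repair began.

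This is the only continuous measure of pulp repair that the article describes. If it is reported under its present name, a similar mean in the two arms would be read as similar barriers, and a shorter or longer mean as a thinner or thicker barrier. Either reading could be wrong. Furcal or root resorption, a change in the visible capping layer, or a layer that is thicker in one arm can each move A-B with no change in any barrier.

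**Working it through.** The article states no expected value, standard deviation or dimension for this measure, so there is no figure to reproduce. The check is to set the definition beside the procedure and then decompose the distance.

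**1. Definition against timing.** The measure is taken on the immediate postoperative film (Measurement of the dentin barrier), and that film is taken straight after treatment (Clinical procedures). No new hard tissue can exist then. A true barrier thickness would be zero at that visit.

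**2. Decomposition.** Write

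A-B = c/2 + b + f

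where c is the thickness of the capping layer (A is its centre, so half counts), b is any new tissue lying on the line, and f is the existing dentin from the chamber floor to the furcation. On the immediate film b = 0, so A-B = c/2 + f, which is above zero whatever the dimensions.

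**3. Illustration.** The dimensions are assumptions: c from 0.5 to 1.5 mm, f from 1 to 2 mm.

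| c (mm) | f (mm) | A-B with no barrier (mm) |
|---|---|---|
| 0.5 | 1 | 0.25 + 1 = 1.25 |
| 1.0 | 1.5 | 0.50 + 1.5 = 2.00 |
| 1.5 | 2 | 0.75 + 2 = 2.75 |

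**4. Difference between arms from the material alone.** If the layers differ in thickness by d, A-B differs by d/2:

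- d = 0.2 mm gives 0.10 mm
- d = 0.5 mm gives 0.25 mm
- d = 1.0 mm gives 0.50 mm

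Randomisation balances f in expectation. It does not balance c, because the layer is part of the treatment: a hand-mixed cement in one arm and a prefabricated three-layer membrane in the other.

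**5. Change from the immediate film.** With subscripts 0 for the immediate film and t for follow-up,

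change = (c_t - c_0)/2 + b + (f_t - f_0)

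Subtraction removes the baseline offset and, if the visible layer is stable, the layer term of step 4. It leaves any loss at the furcation: an assumed loss of 0.5 mm lowers A-B by 0.5 mm with b unchanged. Furcal impairment, internal or external resorption and advanced rhizolysis are all radiographic criteria under Clinical and radiographic evaluations, so the protocol itself looks for such events.

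**6. Where the line runs.** The teeth are primary molars (Eligibility), the coronal pulp is removed, and both materials sit on the stumps. In a molar the stumps lie at the canal openings and the furcation lies between the roots. The natural inference is that A-B crosses the chamber floor and that tissue formed at the stumps contributes little to b. This is anatomy applied to the stated procedure; no figure in the article measures it.

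**The case against.** The choice is deliberate. The Discussion gives a reason for it, and the landmarks carry a citation to a source that is not at hand and that may describe A-B as a proxy or a change score. A non-zero first reading is an ordinary baseline, which the paired test removes within groups. Furcal and resorptive changes are scored separately, so they would be visible beside A-B. Measuring at the canal openings instead would bring back the root overlap that the method was chosen to avoid.

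Much of this stands. The positive baseline does limited harm once change is analysed, and the statistical analysis plan, which is not shown, may specify change for the between-group test. Measurement at the canal openings is a trade-off and cannot be presented as a plain improvement. But neither the stated reason nor the citation alters what the two landmarks enclose, and the outcome is still named as a barrier thickness.

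A reader might go further and infer that A-B cannot respond to a barrier at all, so that a complete barrier and no barrier would give the same reading. The documents do not establish that. It requires A and B to be fixed, whereas each film is marked afresh and A moves if the visible layer changes; and the article does not say where hard tissue forms or how it projects on a two-dimensional film. Nor does the Discussion admit that the method fails: it offers a rationale for using it.

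**Conclusion.** The point holds as a matter of labelling and interpretation. A-B includes part of the capping material and existing dentin, is positive before a barrier can exist, and is not bounded by landmarks at the site of repair. The first two statements follow directly from the definition and the timing of the films. That the line largely misses tissue at the stumps is an inference.

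The sizes in the working (a baseline of 1.25 to 2.75 mm; a shift between arms of 0.10 to 0.50 mm from layer thickness alone) rest wholly on assumed dimensions and show direction and order only. A claim about how many millimetres A-B measures in these teeth would have no support in the article.

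The consequence is confined to this outcome. The null hypothesis and the sample size rest on clinical and radiographic success, and that comparison is untouched. What changes is what may be concluded about barriers: from A-B alone, neither a difference nor its absence shows whether barriers formed or how thick they are.

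**What to change.** - In the Abstract and in Measurement of the dentin barrier, rename the variable *capping material-to-furcation distance*.
- In Statistical methods, state that the between-group test compares change from the immediate postoperative film at 12 and 24 months.
- Report that change beside the furcal and resorption findings from Clinical and radiographic evaluations, so that shortening through loss of tooth substance can be recognised.
- State that no conclusion about the formation or thickness of a dentin barrier will be drawn from this distance alone.

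The cost is a few sentences; no visit, film or reading is added.

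Optionally, the same blinded examiner could score a barrier at the canal openings as present, absent or not readable on the existing scans, as a supportive reading. This costs a second reading of films already taken. Its drawback is missing readings where roots overlap, possibly more often in some tooth types; the article gives no basis for estimating how many.

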### Data collection methods, management, and monitoring

The clinical and radiographic aspects of teeth will be evaluated at 12 and 24 months after procedures. Data will be collected and registered on case report forms by trained researchers blinded to group allocation. Data quality will be ensured by validation checks that include missing data. Clinical and radiographic data will be inserted directly in clinical and radiographic evaluation forms. The data of the scanned x-rays will be entered in Corel Draw version 13 software for further analysis. Data monitoring committee (DMC) will independently check data and report any problem. DMC is independent from the sponsor and competing interests. The data will be monitored by an independent clinical research assistant, one statistician, and one dental surgeon. No interim analysis beyond that described above is planned.

### Ancillary and post-trial care

After completing the study, participants will continue to receive dental treatments, if needed, in the Pediatric Dentistry Clinics of University of Sao Paulo, Bauru, Sao Paulo, Brazil.

## Discussion

Many pulpectomy and extractions could be avoided whether pulp regeneration therapies would be tailored for primary teeth [4, 38]. Vital pulp therapy is routinely practiced for the treatment of primary teeth focusing on the regeneration of the dentin-pulp complex [4, 17–19, 38]. Thus, the capping material placed on the remaining pulp stumps should have the capacity of inducing the proliferation of stem and angiogenic cells of the pulp to replace the affected ones [38]. In this context, a bioactive material releases calcium ion, induces electroconductivity, produces hydrogen and calcium, and forms an interfacial layer between the material and the dentin with apatite crystals onto the material surface [12, 13].

According to some systematic reviews and meta-analysis, MTA has higher success rates compared to other materials [6–9]. MTA is a bioactive bioceramic endodontic cement, that is, MTA produces hydroxyapatites after hydration and induces a regenerative response by forming nanocrystals [39]. The presence of calcium trisilicate and disilicate accounts for this bioactivity [12, 40, 41]. Despite its biocompatibility, MTA has some drawbacks such as longer setting time, difficult handling, and potential for tooth discoloration [11–13].

To overcome these MTA drawbacks, different materials can be used. The current tissue bioengineering trends aim at replacing the injured cells or stimulating the growth of the injured tissue through biomaterials [4]. Accordingly, future studies should verify the effectiveness of the developing biomaterials [4, 25, 26, 38]. A chitosan-based pulp dressing material seems a wise choice and provides a wise potential once this material exhibits a number of beneficial properties [23, 42]. The chitosan concentrations used to formulate the membranes are biocompatible, safe, and without side effects for humans’ tissues [25, 26]. Also, several biomedical and dental studies employing chitosan as the primary principle of membranes for tissue repair demonstrate an extensively explored field such as tablets, drug delivery systems, and more recently in tissue engineering, showing good results of biocompatibility in contact with human cells [23, 27, 43, 44].

The limitations of the present study include the disadvantages of noncompliance and high dropout rates, and the obstacle to control the period of follow-up. These disadvantages result in investigations with small sample size and the follow-up time. Further studies should be conducted, and the results should be confirmed through longer-term follow-up periods. The measurement of the dentin barrier after procedures of pulp therapy may have some limitations. This method will be used to avoid mistaken measurements due to the difficulty in evaluating the exact thickness of the dentin barrier and the overlapping of the radiographic image of the roots. One other bias of this present study will be the blinding of the operator. Although it is not possible to blind the operator during capping material application, we believe that this will not interfere in the study outcomes. Therefore, this study protocol aims at new perspectives of vital pulp therapy of primary teeth by employing new easy-handling, low-cost materials to keep viable the pulp tissue capable of regenerating and maintain the physiological process of deciduous tooth exfoliation.

## Trial status

This trial, with protocol version 1, began in November 2019 and is still ongoing; patient recruitment is not yet complete and is planned to continue until September 2020. The first patient was included in December 2019, and the study period will end in September 2022.

## Data Availability

The datasets generated and/or analyzed during the current study will be available from the corresponding author on reasonable request.
